####  Procedure for unblinding if needed{17b}

In the context of clinical research, the act of unblinding may be deemed justifiable under certain circumstances, including the following:Emergencies or adverse events: Unblinding may be warranted when a participant encounters a severe adverse event or medical emergency. In such instances, awareness of the specific intervention received becomes essential for informed and appropriate medical management.Completion of the study: Upon the culmination of the study, participants are frequently apprised of the particulars regarding the nature of the intervention they were assigned. This post-study disclosure is a customary practice designed to ensure transparency and provide participants with comprehensive insights into the conducted research.Unblinding requests: In the event of a participant’s request to know their intervention assignment, the research team will disclose this information following the trial procedures and ethical considerations.

### Interventions {11a}

Upon obtaining signed informed consent from the subject, the following process is executed (Figs. 2 and 3):Screening periodAfter the patient enters the endoscopy examination room and decides to undergo upper gastrointestinal endoscopy treatment, the researcher collects information on the patient’s demographics, medical condition, and proposed examination plan. An independent anesthesiologist evaluates the patient’s examination plan before randomization, and eligible patients are selected based on the inclusion/exclusion criteria. Patients should be assessed by researchers who are knowledgeable about the protocol and authorized to do so in a quiet environment. The study’s purpose, methods, potential benefits, and risks must be thoroughly explained to the patient and/or their representative, and data collection and follow-up procedures before, during, and after the examination must be detailed.The researchers should address the patient and their family members’ questions in detail, allowing sufficient time for consideration and obtaining informed consent from the patient and/or their representative on a completely voluntary basis. The assessor must not be involved in the patient’s examination, sedation, or anesthesia management plan. *Sedation management plan*: An anesthetist with the title of attending physician or above will implement the sedation and anesthesia plan. The patient enters the endoscopy consultation room’s preparation area and takes 10 g of lidocaine gel (containing 0.2 g of lidocaine) orally 5 min before the examination. The patient assumes a left lateral position on the treatment bed in the endoscopy consultation room, and basic vital signs including noninvasive blood pressure (NIBP) of the right upper arm, electrocardiogram, and pulse oxygen saturation (SpO_2_) are monitored. Oxygen is continuously administered through a 4L/min nasal cannula throughout the procedure until the patient fully awakens. A venous line is established, and sufentanil 5 μg is administered intravenously. Patients scheduled for upper gastrointestinal endoscopy are randomized to receive one of two sedative drug infusions: propofol in group C or remimazolam in group R. In group C, patients receive a single dose of propofol at 1.5 mg/kg, while in group R, patients receive a single dose of remimazolam at 0.15 mg/kg, both administered within 1 min. According to the domestic expert consensus, moderate or deep sedation is required for upper gastrointestinal endoscopic examination. Therefore, the MOAA/S score (Appendix 2) should be assessed 1 min after propofol injection. If the MOAA/S score is greater than 3 points, propofol 0.5 mg/kg or remimazolam 0.05 mg/kg should be administered repeatedly until the MOAA/S score is less than or equal to 3 points, with a maximum of five repetitions. The VAS (Appendix 3) should be assessed during propofol or remimazolam injection.*Intraoperative monitoring*: Intraoperative monitoring includes electrocardiogram, noninvasive blood pressure, pulse oxygen saturation, and, when necessary, body temperature, urine output, end-tidal carbon dioxide concentration, and blood glucose levels.*Sedation maintenance plan*: During the examination procedure, the chief anesthesiologist determines whether to administer additional trial medication based on the surgical process and duration. Propofol (0.5 mg/kg) or remimazolam (0.05 mg/kg) is administered in single doses with a minimum interval of 1 min to maintain the patient at an appropriate level of sedation (MOAA/S score ≤ 3). If sedatives are insufficient to maintain appropriate sedation during the examination, the investigator may decide to use alternative sedative agents (midazolam).*Examination plan*: Based on the type of lesion, the endoscopic examination of the upper digestive tract in our hospital may include, but is not limited to, upper gastrointestinal inflammation, tumors, ulcers, polyps, gastroesophageal varices, and gastrointestinal strictures. According to the type of endoscopic treatment of the upper gastrointestinal tract, it may include, but is not limited to, sclerotherapy, argon plasma coagulation, high-frequency electrocautery, and submucosal dissection. Various procedures are conducted following established clinical surgical protocols. *Postoperative management plan*: After the examination or procedure, the patient enters the anesthesia recovery room, where continuous monitoring of ECG, noninvasive blood pressure, and oxygen saturation occurs. The MOAA/S score is assessed every 5 min. Once the score reaches 5 points for three consecutive assessments, and blood pressure, heart rate, and oxygen saturation are normal and stable, the patient can leave the recovery room accompanied by a companion. In case of special circumstances, refer to the adverse event handling procedures.

**Fig. 2 Fig2:**
[figure not shown]
Technical RoadmapA

**Fig. 3 Fig3:**
[figure not shown]
Technical RoadmapB

### Criteria for discontinuation or modification of allocated interventions{11b}

We do not plan to intentionally alter the specified interventions. However, it should be emphasized that participation in all the interventions detailed in the program is at the discretion of the individual participants. They have the freedom to choose whether to engage in or omit any of the intervention measures. Thus, if participants perceive any aspect of the intervention as less beneficial, they may opt out of that component.

The attending anesthesiologist has the authority to discontinue a participant’s involvement in the trial at any point for medical reasons. This responsibility, including the assessment of factors such as adverse reactions, lies solely with the attending anesthesiologist. Furthermore, participants have the right to withdraw from the study whenever they wish by revoking their consent.

### Strategies to improve adherence to interventions {11c}

Comprehensive informed consent process: During the recruitment phase, ensure the provision of clear, detailed, and easily comprehensible informed consent documents to participants. This documentation should encompass information on research objectives, procedures, potential risks, and benefits. Guarantee that participants possess a thorough understanding and willingly consent to participate in the study.Collaborative efforts within the medical team: Ensure effective collaboration among members of the medical team to collectively address issues that may impact adherence. A unified medical team can adeptly tackle challenges related to participant compliance.Anonymity and privacy safeguards: Reassure participants about the protection of their data and strive to ensure anonymity whenever feasible. This approach serves to alleviate concerns and bolster participant trust in the research process.

These strategies aim to enhance participant understanding, foster collaboration within the medical team, and prioritize the safeguarding of participant data and privacy.

### Relevant concomitant care permitted or prohibited during the trial {11d}

In our study, the endoscopic examinations and treatments are conducted following standard care and interventions as per routine clinical practice. This approach ensures that all procedures align with the established norms of medical care for such procedures.

Additionally, it is important to note that any concomitant treatments or interventions that fall under the exclusion criteria of our trial are strictly prohibited. We have implemented this prohibition to maintain the integrity of the trial and to ensure that the outcomes are not influenced by external variables. This includes any interventions that directly result from or are related to the exclusion criteria.

### Data Collection {18a}

#### Preoperative data collection

The baseline data collection will be conducted when the subjects enter the gastroscopy treatment room and are in a calm state. Upon obtaining informed consent from the subjects, the preoperative interviewer shall complete the baseline data collection as follows:

Demographic information, including name, gender, date of birth, height, and weightPreoperative diagnosis, including comorbidities (such as coronary heart disease, history of cerebrovascular accidents, hypertension, diabetes, chronic obstructive pulmonary disease, abnormal liver and kidney function), medication history (ACE inhibitors, ARBs, β-blockers, insulin, metformin, aspirin, clopidogrel, salbutamol, aminophylline, ipratropium bromide, etc.), smoking and smoking cessation history, and history of anesthesia and sedation.Severity of the disease or physical condition, ASA classification (refer to Appendix 1, with a requirement for participants to be classified as ASA III–IV).Baseline values of NIBP, HR, and SpO_2_ before the examination.Upper gastrointestinal endoscopy examination and planned examination location (esophagus and/or stomach).

#### Intraoperative data collection

Starting from the administration of intervention drugs, test the MOAA/S score every 30 s for 5 min, and then test every 2 min until the examination and operation are completed.

Record the time interval (seconds) from the start of intervention drugs to the time when MOAA/S score ≤ 3.

Record the presence of injection pain during the administration of intervention drugs using a visual analog scale (VAS) ranging from 0 to 10, where 0 indicates no pain and 10 indicates maximum pain (see Appendix 3). This assessment is conducted 1 min and 20 min after the start of drug administration or every 5 min thereafter if the patient remains sedated until the patient can complete the scale.

Record the MOAA/S score when the endoscope is smoothly placed in the esophagus.

Record the dose of intervention drugs used when the endoscope is smoothly inserted into the esophagus (including additional and rescue drugs, types, frequency, and dosage).

Measure NIBP every 3 min from the start of intervention drugs until the end of the examination.

Continuously monitor SpO_2_ until the end of the examination and record the minimum SpO_2_ during the procedure.

Record the total duration of the examination and operation (in minutes).

Record the types, frequency, and dosage of additional or rescue drugs during the examination, along with the corresponding time points.

Record the number of interruptions during the examination and the reasons for interruption, along with the time elapsed since drug administration began.

Record adverse events and their corresponding times during the period from drug administration to the end of the examination (see 1.10), such as respiratory spasms, reflux aspiration, coughing during endoscope entry into the oral cavity, SpO_2_ below 90% due to repeated coughing, SpO_2_ below 90% due to respiratory depression, positive pressure mask ventilation, jaw support-assisted ventilation, systolic blood pressure < 80 mmHg, or the need for vasopressors, systolic blood pressure ≥ 180 mmHg, *HR* ≤ 55 beats/min, *HR* > 100 beats/min, and the frequency and conditions of severe arrhythmias.

Operator satisfaction score (0–10 points, with 0 indicating very dissatisfied and 10 indicating very satisfied).

Post-examination diagnosis: Upper gastrointestinal inflammation, tumors, ulcers, polyps, esophagogastric varices, gastrointestinal stenosis, etc. and surgical procedures: endoscopic hemostasis (clipping, electrocoagulation, band ligation), sclerotherapy, argon plasma coagulation, high-frequency electrocautery, etc.

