#### Secondary outcomes

*Sedation efficacy outcomes*: (1) MOAA/S score after single administration; (2) time required to achieve a MOAA/S score of ≤ 3 points following single administration; (3) for patients not achieving adequate sedation depth after a single dose and documentation of additional medication doses and frequency; (4) total amount and number of additional administrations of remimazolam or propofol in both groups during the entire course of upper gastrointestinal endoscopy and treatment; (5) duration from the initiation of medication injection to the completion of upper gastrointestinal endoscopy and treatment; (6) type, frequency, and dose of alternative or additional remedial drugs required when the upper limit of supplementary dosage is exceeded; and (7) operator satisfaction.

*Consciousness recovery outcomes*: (1) Time to full awakening; (2) use of sedative antagonist flumazenil, if applicable; (3) assessment of patients’ recall of upper gastrointestinal endoscopy and treatment process using the Brice questionnaire (Appendix 4) after awakening; (4) duration of patients’ recovery; and (5) overall patient satisfaction.

*Safety outcomes*: (1) Incidence of hypertension or hypotension during the procedure and in the recovery room, (2) incidence of tachycardia or bradycardia during the procedure and in the recovery room, (3) incidence of low oxygen saturation during the procedure and in the recovery room, (4) airway intervention rate during the procedure and in the recovery room, (5) incidence of coughing within 1 min after endoscope insertion, (6) incidence of coughing during upper gastrointestinal endoscopy and treatment, and (7) incidence of injection-related pain.

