#### Efficacy evaluation{20a}

Primary endpoint evaluation: In the intention-to-treat (ITT) analysis population, a chi-square test will be used to compare the success rates of patients completing endoscopic examination and treatment between the two groups. Simultaneously, a generalized linear model will be employed to calculate the unadjusted and adjusted absolute risk differences (ARD). Adjusted variables will encompass stratification indicators (invasive procedures during upper gastrointestinal endoscopy and treatment), BMI, age, concurrent respiratory diseases, concurrent cardiovascular and cerebrovascular diseases, liver and kidney function abnormalities, and operator experience. Secondary effect sizes will be presented as odds ratios (OR) with a 95% confidence interval.

Evaluation of secondary endpoints: For the intention to treat (ITT, includes all participants who were randomly assigned, regardless of whether they completed the entire study or fully adhered to the study protocol) population, chi-square test or *t*-test will be employed for comparative analysis based on variable nature (e.g., categorical variables like low oxygen saturation, hypotension, tachycardia, intraoperative awareness, recovery delay, or continuous variables such as MOAA/S, NIBP, HR, and SpO_2_). Results will be reported as odds ratios (OR) and 95% confidence intervals using a generalized linear model. Time event variables (e.g., time to achieve a MOAA/S score of ≤ 3 points after a single dose) will be analyzed using Cox regression to describe and compare the two groups, generate Kaplan-Meier curves, express results as hazard ratios (HR), and report a 95% confidence interval.

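### Onset time is named and analysed as a single-dose outcome, but the time recorded runs on through the top-ups

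*Protocol article*

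**What the plan says.** All four places are in the protocol article.

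- **Secondary outcomes**, sedation efficacy item (2): the time needed to reach MOAA/S ≤ 3 "points following single administration". Items (1), (3) and (4) cover the score after the single administration, the extra doses of patients not adequately sedated by it, and the total additional drug given.
- **Efficacy evaluation {20a}**: the same outcome is the worked example of a time-to-event variable. Time to MOAA/S ≤ 3 "points after a single dose) will be analyzed using Cox regression to describe and compare the two groups", with Kaplan-Meier curves and a hazard ratio, in the paragraph that places secondary endpoints in the ITT population.
- **Intraoperative data collection**: "Record the time interval (seconds) from the start of intervention drugs to the time when MOAA/S score" ≤ 3. This is the only onset time collected, and nothing in the item refers to top-ups.
- **Interventions {11a}**: the first doses are "both administered within 1 min", and the score "should be assessed 1 min after propofol injection". If it is above 3, "propofol 0.5 mg/kg or remimazolam 0.05 mg/kg should be administered repeatedly until the MOAA/S score is less than or equal to 3 points", with a cap of five repetitions.

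**The concern.** The outcome's name and its analysis refer to one dose. The collected variable refers to a regimen of one to six doses. The link between them matters because a top-up is triggered by failure of the first dose and is repeated until the event occurs or the cap is reached. If the recorded interval is used as it stands, a patient who did not respond to the first dose but responded to a later one is counted as a single-dose event with a longer time.

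Two things are at stake. The curves and hazard ratio would carry a single-dose label that is untrue for some patients. And a drug whose first dose fails more often would be partly rescued by its own top-ups, so a real difference in first-dose performance would look smaller.

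**Working it through.** **Plan's own figure.** The protocol gives no figure for this outcome. Its sample size rests on the primary outcome and reproduces: (1.960 + 0.842)² × 2 × 0.79 × 0.21 / 0.10² ≈ 260.4, so 261 per arm and 522 in total; 261 × 1.1 = 287.1, so 288 per arm and 576. The present point does not touch it.

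**When does a recorded time stop being a single-dose time?** The initial injection takes at most 60 s and the score that decides on a top-up is taken 60 s later. The text names only propofol for this assessment; I assume it applies to both arms, since the top-up rule does. The first top-up is then due at 60 + 60 = 120 s after drug start at the latest. If the intervention section is followed, nearly every recorded interval beyond about 2 min is a multi-dose time.

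**How much drug can precede the event?** Only for a patient given all five top-ups:

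- propofol: 1.5 + 5 × 0.5 = 4.0 mg/kg; 4.0 / 1.5 = 2.67
- remimazolam: 0.15 + 5 × 0.05 = 0.40 mg/kg; 0.40 / 0.15 = 2.67

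**Effect on the hazard ratio.** The documents give no first-dose or top-up response rates, so this is illustration only. Assumptions: 288 per arm; first-dose responders spread evenly over 60, 90 and 120 s; top-ups at 120, 180, 240, 300 and 360 s; responders to a top-up reach the target 30 or 60 s later; 60 simulated trials per scenario; Cox model with Efron ties. The hazard ratio is remimazolam (R) against propofol (C).

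| First-dose success C / R | Response per top-up | As recorded | Censored at first top-up |
|---|---|---|---|
| 90% / 90% | 70% | 1.00 | 1.00 |
| 90% / 70% | 70% | 0.65 | 0.58 |
| 90% / 50% | 70% | 0.45 | 0.35 |
| 80% / 60% | 50% | 0.70 | 0.61 |
| 70% / 90% | 70% | 1.52 | 1.66 |

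On the log scale the contrast shrinks by roughly a fifth to a quarter: ln 0.65 / ln 0.58 = 0.79, ln 0.45 / ln 0.35 = 0.76, ln 0.70 / ln 0.61 = 0.72, ln 1.52 / ln 1.66 = 0.83. The direction never changes.

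In this set-up every first-dose event falls at or before 120 s, so keeping topped-up patients as non-events beyond 120 s gives the same hazard ratio as censoring them there.

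**Effect on the curves.** The share with an event after up to five top-ups is 1 − (1 − first-dose success) × (1 − top-up response)⁵. For 80% / 60% with 50% per top-up this is 1 − 0.2 × 0.5⁵ = 99.4% and 1 − 0.4 × 0.5⁵ = 98.8%. The 20-point gap in first-dose success falls to under one point by the end of the recorded curves.

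**The case against.** The strongest reply has three parts.

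*The data-collection list is not an analysis rule.* It names a raw item. Both places that define or analyse the outcome restrict it to a single dose, and how topped-up patients are handled may be settled in an analysis plan that is not shown. This stands in part. A reader might infer that the protocol instructs analysts to credit top-up successes to the first dose. It does not say so; that result follows only if the recorded interval is used unchanged. What remains is that the protocol names one onset time, and it does not match the outcome.

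*The wording may name only the time origin.* On that reading, following a single administration means counting from the first bolus, and nothing conflicts. But the result would still be presented as a single-dose time when for some patients it is not.

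*First-dose failure is visible elsewhere.* Items (1) and (3) do show it, and the first-dose proportion follows from them. So a reader should not infer that a difference in first-dose success would be hidden altogether. Those items do not, however, take topped-up patients out of outcome (2).

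Two stronger readings also fail. That almost every patient must end with an event is not established: top-ups are capped at five and no response rate is given. And the 2.67-fold dose is a ceiling, not a typical exposure.

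**Conclusion.** The mismatch is in the text and should be corrected, as a matter of one secondary outcome. The definition and analysis say single dose; the recorded time takes in whatever top-ups the intervention section triggers. Used as recorded, it mislabels the curves and attenuates any single-dose contrast moderately: in the assumed scenarios with unequal first-dose success the log hazard ratio shrinks by about 17% to 28%, and with equal first-dose success there is no effect. These sizes rest on assumed response rates and one-minute top-up spacing. The existence of the mismatch rests on neither. The primary endpoint, the margin and the sample size are not affected.

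**What to change.** 1. For outcome (2), count the event only if MOAA/S ≤ 3 is reached before any supplemental dose. Keep topped-up patients in the ITT analysis as not having reached it. They can be identified from the recorded frequency and dose of additional drug up to insertion, together with the 30-second scores.
2. Report the proportion reaching MOAA/S ≤ 3 on the first dose, by arm, from items (1) and (3).
3. Report the interval as now recorded as a separate outcome, labelled time to target under the titration regimen.
4. If censoring at the first top-up is preferred, add the time of each pre-insertion top-up to the record. The intraoperative list expressly asks for time points only for drugs given during the examination; for drugs up to insertion it names type, frequency and dosage. Such censoring would also be informative, because the top-up is given for non-response, so step 1 is the cleaner choice.

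The choice should be fixed before the data are analysed. Steps 1 to 3 change wording only; step 4 adds one time field. The cost is that single-dose follow-up ends at about 2 min for topped-up patients, so a late response to the first dose alone cannot be seen in them. No change to dosing is implied.

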#### Recovery room data collection

Immediately after the examination, the patient is transported to the recovery room until fully awake.

After entering the recovery room, test the MOAA/S score every 5 min and record it.

Record the time required from the end of the operation to the patient’s MOAA/S score recovering to 5 points (need to reach 5 points continuously for three times, choose the first time with a score of 5).

Measure NIBP every 3 min after entering the recovery room and record it.

Continuously monitor SpO_2_ until the end of the examination and record the minimum SpO_2_ during the procedure.

Adverse events occurring in the recovery room (see 1.10), such as SpO_2_ below 90%, positive pressure mask ventilation, jaw support-assisted ventilation, systolic blood pressure < 80 mmHg or the need for vasopressors, systolic blood pressure ≥180 mmHg, *HR* ≤ 55 beats/min, and *HR* > 100 beats/min

When the subjects meet the discharge criteria, record their anesthesia satisfaction score (0–10 points, with 0 indicating very dissatisfied and 10 indicating very satisfied).

Whether flumazenil was used for antagonism in case of delayed awakening.

When the patient’s MOAA/S score recovers to 5 points, use the modified Brice questionnaire to determine if the patient was aware during the procedure.

Collect information on the operator’s years of experience.

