#### Exploratory analysis {20b}

Subgroup analyses based on patients’ clinical characteristics will be performed in pre-specified post hoc exploratory analyses. Potential factors impacting the examination success rate include BMI, age, the presence of respiratory diseases, cardiovascular and cerebrovascular diseases, liver and kidney dysfunction, alcohol and drug dependence, and operator experience.

Repeated measurement data (e.g., multiple measurements of MOAA/S, NIBP, HR, and SpO_2_) will be analyzed using a generalized additive mixed model (GAMM). The fixed effect will be a stratification indicator (invasive procedures during upper gastrointestinal endoscopy and treatment), and the interaction between groups and time will be evaluated.

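### As stated, the SpO2 recording rules cannot supply the exploratory group-by-time model, and the recovery-room SpO2 rule ends before recovery begins

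*Protocol article*

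**What the plan says.** The relevant text is in five places in the protocol article.

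- **Preoperative data collection** takes one reading of each vital sign: "Baseline values of NIBP, HR, and SpO_2_ before the examination".
- **Intraoperative data collection** schedules sedation scores at half-minute intervals for the first five minutes and two-minute intervals after that. It also schedules blood pressure: "Measure NIBP every 3 min from the start of intervention drugs until the end of the examination". For SpO2 the instruction is: "Continuously monitor SpO_2_ until the end of the examination and record the minimum SpO_2_ during the procedure". Heart rate has no line of its own. It appears, with SpO2 below 90%, among the events covered by: "Record adverse events and their corresponding times during the period from drug administration to the end of the examination".
- **Recovery room data collection** opens with: "Immediately after the examination, the patient is transported to the recovery room until fully awake". It schedules blood pressure every 3 min and then repeats the intraoperative SpO2 sentence word for word. Its adverse-event list includes SpO2 below 90% and the heart-rate thresholds.
- **Interventions {11a}**, in the postoperative plan, describes the recovery room as a place "where continuous monitoring of ECG, noninvasive blood pressure, and oxygen saturation occurs".
- **Exploratory analysis {20b}** states: "Repeated measurement data (e.g., multiple measurements of MOAA/S, NIBP, HR, and SpO_2_) will be analyzed using a generalized additive mixed model". It adds that the group-by-time interaction will be assessed.

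The safety outcomes under **Secondary outcomes** include "incidence of low oxygen saturation during the procedure and in the recovery room".

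**The concern.** A group-by-time model needs several dated values per patient, taken whether or not anything has gone wrong. Of the four variables named for the model, the article gives a timed schedule for two: sedation score and blood pressure. For SpO2 it states a different rule, which keeps one extreme value and no time. A stated recording rule and a stated analysis therefore do not fit together.

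The recovery-room sentence is a separate error. Its window ends with the examination, but the recovery phase starts only after the examination. Followed literally, staff would write down the procedural minimum a second time and no recovery minimum at all.

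Two things are at stake. One is the planned description of how oxygen saturation evolves under each drug. The other is the quality of a recovery-room safety outcome in ASA III–IV patients. Without a recorded minimum, that outcome depends on staff reporting each event. The Blinding section says that the outcome assessors are the unblinded interventionists, although the limitations paragraph of the Discussion says that evaluators will be blinded.

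**Working it through.** No figure in the plan bears on this point, so the check sets the recording rules against the analysis that needs them.

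**Step 1: scheduled timed values per patient during the procedure.** The article gives no procedure length, so D = 10, 20 and 30 min are assumptions. Readings at time zero are not counted.

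- Blood pressure, every 3 min: floor(D/3).
- Sedation score: 10 values in the first 5 min, then one every 2 min: 10 + floor((D − 5)/2).
- SpO2: one minimum, with no time attached, whatever D is.
- Heart rate: no interval stated in the article.

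| Assumed D | Blood pressure | Sedation score | SpO2 | Heart rate |
|---|---|---|---|---|
| 10 min | 3 | 10 + 2 = 12 | 1, undated | none stated |
| 20 min | 6 | 10 + 7 = 17 | 1, undated | none stated |
| 30 min | 10 | 10 + 12 = 22 | 1, undated | none stated |

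**Step 2: can the SpO2 model be fitted?** Adding baseline gives 1 + 1 = 2 SpO2 values per patient, and only the baseline can be placed on the time axis. Event times exist as well, but only for patients who fell below 90%. A series built from them would be selected on the outcome. Dating the minimum would not be enough either, because a value chosen for being lowest is not a sample of the time course. A smooth curve over time, and its difference between groups, cannot be estimated from these data.

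**Step 3: the recovery window.** The order of events is: examination ends, SpO2 rule ends, patient is moved to recovery, recovery recording starts. The SpO2 rule therefore covers none of the recovery period. Interventions {11a} says saturation is monitored continuously there, so the reading is on the monitor, but no stated rule records it unless it is reported as an event.

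**Step 4: which outcomes remain derivable?**

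- Primary composite, SpO2 below 90% during the examination: yes, from the recorded procedural minimum.
- Primary composite, heart rate at or below 55 or above 100: yes, from the listed adverse events with their times.
- Low saturation in recovery: yes as an incidence, from the recovery adverse-event list, but with no recorded minimum to verify it.
- SpO2 in the group-by-time model: no, under the rules as stated.
- Heart rate in the same model: not from the article, and undecided without the full protocol or case report form.

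**The case against.** The best reply is that this is a condensed article. Its data-collection lists refer to a numbered section that is not reproduced, and the study schedule figure and the case report form are not shown. An interval for heart rate, perhaps paired with each blood pressure reading, could be stated there. The model's wording refers to multiple measurements, which suggests that the authors expect serial values. This stands for heart rate: the article's silence does not show that no readings are taken. It is weaker for SpO2, where the article states a rule and that rule yields one value. The rule does not forbid other recordings, so the conclusion is limited to the rules as stated.

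A second reply is that the model is exploratory, that its variables are given only as examples, and that the recovery sentence is a copying slip. All of this is fair and limits the weight of the point. It does not remove the mismatch or supply the missing recovery minimum.

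A reader might go further and infer three things that the documents do not support:

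- **That unrecorded readings are lost.** Data management and monitoring {19} says the case report form is transcribed from original observation records, so upstream sources exist. Whether they hold serial SpO2 and heart rate is unknown.
- **That the primary composite is compromised because SpO2 and heart rate are among its components.** It uses thresholds, which the minimum and the event records can supply.
- **That the t-test listed for heart rate under Efficacy evaluation has no value to test.** Defining that variable is normal content of an analysis plan that is not shown.

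**Conclusion.** The point holds in a limited form. Under the stated rules, SpO2 contributes a baseline value and one undated procedural minimum, plus event times in patients who desaturate. That cannot support the planned exploratory group-by-time model. For heart rate, the article states no interval after baseline, and the full protocol or case report form may fill that gap. The recovery-room SpO2 sentence is wrong as written and contradicts the postoperative plan. Recovery low saturation can still be counted, but only from adverse-event reports.

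The effect is confined to one exploratory model and to the verification of one safety outcome. The primary composite, and any non-inferiority conclusion drawn from it, are untouched. The counts for blood pressure and sedation score rest on assumed procedure lengths. The SpO2 conclusion does not, because its count is one at any length. The correction is worth making because it is cheap and repairs a stated conflict.

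**What to change.** 1. In both the intraoperative and the recovery-room lists, record SpO2 and heart rate on the case report form at each 3-min blood pressure reading already scheduled. If the full protocol already does this for heart rate, cite it.
2. Reword the recovery-room sentence so that a minimum SpO2 is recorded from recovery-room entry to discharge from it, separately from the procedural minimum.
3. Enrolment began in December 2022, so some patients will have been recorded under the present rules. For them, take the series from source records or stored monitor trends where these exist. Where they do not, drop SpO2 from the group-by-time model, and heart rate too if it has no series, and compare minimum SpO2 between groups.

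The cost is slightly more transcription at time points when staff are already recording blood pressure, and an incomplete series for patients already enrolled. These changes affect data capture only; no treatment rule changes.
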